## Objectives

### Main objective

To analyze effectiveness, cost-effectiveness and cost-utility of an intervention based on health coaching and telephone support on quality of life, pain, overweight/obesity and physical activity in patients from Primary Health Care Centres (PHCC) of the Barcelona province suffering from osteoarthritis of the knee, compared with usual care.

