#### Outcomes

The main outcome variable is quality of life as measured by the WOMAC index [26]. Secondary outcomes are: pain [27], weight, physical activity [28] and nutrition [29].

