**Table 2 Tab2:** **Data collection, information sources and follow-up**

**Variables**					**Data collection**				
					**Baseline**	***Follow up from recruitment**			
**Clinical dependent variables**	**Measurement instrument**	**Type of response**	**Scoring (total and per item)**	**Range**	**Before intensive phase**	**After intensive phase**	**3 months**	**6 months**	**12 months**
Qual ity of Life	WOMAC (Batl le, 1999)	Likert (0=none to 4=very much)	TOTAL=24 17= functional l imitation 5=pain 2= sti ffness	0-96	X	X	X	X	X
Pain	ICOAP (Mai l lafert, 2009)	Likert (0=none to 4=very much)	TOTAL = 11 5= constant pain 6= intermittent pain	0-44	X	X	X	X	X
Weight (in Kg.)*	Scale at the PCC	Quantitative (kg.)	-	0 - ∞	X	X	X	X	X
Physical Activity	IPAQ (Puig, 2012)	Duration + Frequency of Moderate to Intense	TOTAL= 7	0 - 3000 MET	X	X	X	X	X
Physical Activity*	Pedometer	Quantitative	-	0 - ∞					
Nutrition	PREDIMED (Mediterranean Diet Adherence Questionnaire	Dichotomous (YES= 1 point NO= 0 points)	TOTAL = 14 12= frequency of consumption of foods 2= Mediterranean food habits	0-14	X	X	X	X	X
Other Variables									
Socio-demographic									
Age, gender, educational level, work status, number of children	Ad-hoc Questionnaire	Nominal	-	-	-	X			
Clinical				-					
Drug Prescription	Ad-hoc Questionnaire	Nominal	1	-	X	X	X	X	X
Diagnostic tests	Ad-hoc Questionnaire	Nominal	1	-	X				X
Waist Circumference	Ad-hoc Questionnaire	Quantitative (cm.)	1	-	X	X	X	X	X
Height	Ad-hoc Questionnaire	Quantitative (cm.)	1	-	X				X
Comorbidities	Ad-hoc Questionnaire	Nominal	1	-	X	X	X	X	X
Duration of Disease in Years	Ad-hoc Questionnaire	Quantitative (years)	1	-	X				
Duration Knee Osteoarthritis in	Ad-hoc Questionnaire	Quantitative (years)	1	-	X				
Costs-related			-						
Direct Medical			-						
Cost of coaching in osteoarthrosis	Ad-hoc Questionnaire	Quantitative (euros)	-	-	X	X	X	X	X
Cost of visits to the GP	Ad-hoc Questionnaire	Quantitative (euros)	-	-	X	X	X	X	X
Cost of visits to the nurse	Ad-hoc Questionnaire	Quantitative (euros)	-	-	X	X	X	X	X
Cost of visits to the physiotherapist	Ad-hoc Questionnaire	Quantitative (euros)	-	-	X	X	X	X	X
Cost of visits to special ist MD	Ad-hoc Questionnaire	Quantitative (euros)	-	-	X	X	X	X	X
Cost of Medical Tests	Ad-hoc Questionnaire	Quantitative (euros)	-	-	X	X	X	X	X
Cost of Pharmacological	Ad-hoc Questionnaire	Quantitative (euros)	-	-	X	X	X	X	X
Operating Costs of the PCC	Ad-hoc Questionnaire	Quantitative (euros)	-	-	X	X	X	X	X

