#### Analyses of the economic evaluation

A descriptive analysis of costs and use of resources will be carried out for each study group and these groups will be compared (Table 2).

The time horizon will be of 12 months. The discount rate will be 3%. The incremental cost-effectiveness ratio will be calculated as the difference in the mean costs between both groups divided by the difference between effects of both groups. Health utilities will be calculated through the WOMAC index adjusted by time. The incremental cost-utility ratio will be calculated dividing the difference in mean total costs in both groups by the differences of QALYs of both groups. Acceptability curves will be calculated to determine if the intervention is cost-effective compared with standard clinical practice. An analysis of sensitivity with different discount rates and costs will be carried out to verify the robustness of results.

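### QALYs are to come from WOMAC, a score without preference weights, with no utility instrument collected and no conversion stated, so the cost-utility result depends on an unspecified and untested step

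*Protocol article*

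**What the plan says.** The main objective in the Protocol article is "To analyze effectiveness, cost-effectiveness and cost-utility of an intervention based on health coaching and telephone support", so cost-utility stands beside effectiveness. The section on analyses of the economic evaluation gives one sentence on where utilities come from: "Health utilities will be calculated through the WOMAC index adjusted by time". It then defines the cost-utility ratio as "dividing the difference in mean total costs in both groups by the differences of QALYs of both groups". On timing it says "The time horizon will be of 12 months", with a 3% discount rate. Its sensitivity analysis varies discount rates and costs and nothing else.

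WOMAC is also the primary endpoint: "The main outcome variable is quality of life as measured by the WOMAC index". Table 2 records it as 24 items (17 function, 5 pain, 2 stiffness), each scored "Likert (0=none to 4=very much"), with a range of 0 to 96. It is collected at baseline, after the intensive phase (1 month) and at 3, 6 and 12 months. The section on other variables presents Table 2 as the list of study variables and instruments. The remaining clinical outcomes there are ICOAP pain, weight, physical activity (IPAQ and pedometer) and Mediterranean diet adherence.

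**The concern.** A QALY is time weighted by a utility, and a utility needs two things: weights that reflect preferences between health states, and a scale on which full health is 1 and death is 0. The WOMAC described in Table 2 has neither. It adds up symptom and function items with equal weight, and it rises as the patient gets worse, whereas a utility falls. Some conversion must stand between the score and the QALY, and the article does not say what it is.

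This is more than missing detail. The article names a source for the utilities, and that source does not yield utilities by itself. The instrument list offers no alternative. A later analysis plan can supply a formula, but it cannot recover preference data that no visit collected.

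What is at stake is one part of the main objective and the policy use of the result. The abstract and the Discussion both tie entry into clinical guidelines to showing cost-effectiveness and cost-utility.

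**Working it through.** No figure in the article bears directly on this point, so the check sets the sections side by side and then illustrates how much the missing step can matter.

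**1. What the score is.** Table 2 gives 17 + 5 + 2 = 24 items, each scored 0 to 4, and 24 × 4 = 96. The stated range reproduces as a plain sum, so no item carries a special weight. Because 0 means none, a higher total is worse.

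**2. What else is collected.** None of the other outcomes in Table 2 or in the Outcomes section is presented as a utility measure.

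**3. How far the conversion can move the result.** Inputs from the article: a 5-point target difference (Sample size), the assessment times (Table 2) and the 12-month horizon. Inputs that are assumptions:
- the difference is 0 at baseline, 5 at 1 month, and 5 from then to 12 months;
- utility is linear in WOMAC, with a total span *s* between scores 0 and 96;
- the incremental cost is EUR 500 per patient.

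Area under the difference, by trapezoids:

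(1/12) × (0 + 5)/2 + (11/12) × 5 = 0.208 + 4.583 = 4.79 point-years.

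QALY gain = (4.79/96) × *s* = 0.0499 × *s*.

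| Assumed span *s* | QALY gain | Cost per QALY at an assumed EUR 500 |
|---|---|---|
| 0.3 | 0.015 | about EUR 33,400 |
| 0.5 | 0.025 | about EUR 20,000 |
| 0.7 | 0.035 | about EUR 14,300 |
| 1.0 | 0.050 | about EUR 10,000 |

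A span of 1.0 is a plain rescaling of the sum score. From the top row to the bottom row the ratio changes by 1.0/0.3 = 3.3, with the trial data held fixed. That factor does not depend on the EUR 500.

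**4. What the cost-utility ratio adds.** Under any linear conversion it equals the cost per WOMAC point-year multiplied by 96/*s*. Here that is EUR 500/4.79 = EUR 104 per point-year, and 104 × 96/*s* gives the table again, up to rounding. All that separates the cost-utility ratio from this cost per WOMAC point-year is the choice of *s*, which the article leaves open.

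**5. Whether the planned sensitivity analysis would show this.** With a 12-month horizon, discounting at 3% changes even an amount falling at month 12 by only 1 − 1/1.03 = 2.9%. Varying costs moves the numerator only. Neither touches the conversion.

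**The case against.** The strongest reply is that the wording does not say the raw sum is used as a utility. Utilities are to be calculated *through* WOMAC, which fits a WOMAC-to-utility mapping followed by weighting over time. A reader might infer that raw scores will be multiplied by time, giving point-years with the wrong sign, but the article does not state that procedure. This part of the reply stands.

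A reader might also conclude that the cost-utility objective cannot be met with the planned data. That goes too far. WOMAC is measured at five time points, so an externally estimated mapping could turn it into a utility curve. The documents do not show whether a suitable mapping exists for this population, so neither possibility can be asserted.

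Nor do all acceptability curves fail. The article defines a cost-effectiveness ratio per unit of effect, and curves on that scale remain valid. It names no cost-per-QALY threshold.

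Finally, a journal article condenses, and the full protocol may hold the conversion formula. That is fair for the formula. It does not cover the instrument schedule, which the article presents as the study's list and which contains no preference-based measure. Nor does it cover the sensitivity analysis, whose stated scope leaves out the utility derivation.

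**Conclusion.** The concern holds in a limited form. Utilities, and therefore the QALYs in the cost-utility part of the main objective, are to be derived from a condition-specific score that, as Table 2 describes it, has no preference weights and no 0-to-1 anchoring. No preference-based instrument is listed, no conversion is stated, and the planned sensitivity analysis does not test one.

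The illustrated size is a more than threefold range in cost per QALY. It rests on assumed linear spans of 0.3 to 1.0 and an assumed course of the 5-point difference, so it shows sensitivity and does not estimate the error in this trial. A fixed linear conversion, oriented so that lower WOMAC means higher utility, would not change the direction of the QALY difference, only its scale. A non-linear conversion would also make the gain depend on where patients lie on the scale.

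The primary WOMAC analysis, the sample size and the cost-effectiveness ratio are untouched. The point needs settling before baseline assessments, because uncollected utility data cannot be obtained afterwards.

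**What to change.** **Preferred.** Add a short preference-based questionnaire with a Spanish value set (EQ-5D is one example) at the five assessments already scheduled. Compute QALYs as the area under each patient's utility curve over 12 months, and adjust the group comparison for baseline utility. Replace the WOMAC sentence in the economic section accordingly. The cost is a few minutes per existing interview and a small amendment.

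**If no questionnaire is added.** Prespecify an externally estimated WOMAC-to-utility mapping and name its source. Carry its prediction error into the uncertainty of the cost-utility ratio and of any QALY-based acceptability curve, and vary the mapping in the sensitivity analysis alongside discount rates and costs. This changes analysis wording only. The price is that the result inherits the mapping's error and its fit to this population.

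**If no suitable mapping exists.** Replace the cost-per-QALY claim with cost per WOMAC point, and amend the main objective and the statements about guideline uptake to match. This costs no data collection, but the cost-utility claim is given up.

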#### Statistical analysis

Data will be analyzed on an intention-to-treat basis following CONSORT CLUSTER criteria to avoid bias by incomplete datasets. Missing values will be replaced by multiple imputation methods. The non-response bias will be monitored and evaluated during follow up. According to the distribution of the variables, descriptive analysis will be carried out using the mean (standard deviation), median (interquartile range) or frequency (percentage).

For comparisons within and between the intervention and control groups we will use Student t-tests for independent and paired data, McNemar, Chi-Square, Fisher’s Exact test, analysis of variance and the corresponding non-parametric tests when appropriate.

To evaluate the effectiveness of the intervention between both groups during follow up, the change in the intervention group minus the change in the control group, as well as the standardized effect size (SES) will be calculated. SES will be calculated as the mean difference between both groups divided by the standard deviation of the control group. To detect differences within each group, the difference between the means at baseline and at each follow up time and the effect size or standardized response mean (SRM) following Kazis’method will be calculated [32]. The SRM will be calculated as the mean change divided by the standard deviation of the change. To evaluate SRM and SES we will use Cohen’s rule, which classifies effect size as small (0.2-0.5), medium (0.5-0.8) and large (>0.8).

We examined the effects of intervention over all time points using mixed-effects models on repeated measures.

Multilevel ordered logistic regression will be used for the response variable “physical activity”, in which patients are categorized in three levels: low: <600 METs. min/week; moderate: > = 600 and <1500 METs min/week; high: between 1500 and 3000 METs min/week.

The PHCC will be considered a random effect. The intraclass correlation coefficient will be calculated to determine which percentage of variability in the response is due to the PHCCs. The final models will be adjusted for potential confounders and relevant clinical variables. Interactions and colinearity will be evaluated [33]. Significance level of the model has been set at 5%. The statistical packages SPSS for Windows, v.21 (IBM SPSS Inc., Chicago, IL) and Stata/SE v.12 for Windows (StataCorp. LP, TX) will be used for statistical analysis.

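### The economic section defines cost and QALY differences between arms without saying that the baseline costs and baseline WOMAC it collects are used, which leaves the result open to chance imbalance between 9 v 9 centres and loses precision

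*Protocol article*

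**What the plan says.** The section on analyses of the economic evaluation sets out its own estimators.

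- Cost-utility: "The incremental cost-utility ratio will be calculated dividing the difference in mean total costs in both groups by the differences of QALYs of both groups".
- Cost-effectiveness: "difference in the mean costs between both groups divided by the difference between effects of both groups".
- Source of the QALYs: "Health utilities will be calculated through the WOMAC index adjusted by time". No mapping from score to utility is given.
- Sensitivity analysis: "An analysis of sensitivity with different discount rates and costs will be carried out to verify the robustness of results". Baseline adjustment is not listed.

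The Statistical analysis section is more specific about the clinical outcomes. It defines effectiveness as "the change in the intervention group minus the change in the control group", makes the centre a random effect, and says "The final models will be adjusted for potential confounders and relevant clinical variables". Neither section says whether this model also covers costs and QALYs.

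Table 2 schedules WOMAC and every cost item at baseline, after the intensive phase, and at 3, 6 and 12 months. The Randomization section describes a computer-generated sequence of centres and mentions no stratification or matching.

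**The concern.** A time-weighted QALY total is built from levels of health, not from changes. If one arm starts with worse WOMAC scores, its total tends to be lower whatever the intervention does. A change-minus-change analysis subtracts the baseline score; a plain difference in QALY totals does not. Costs raise the same issue if patients who used more care before entry go on using more, and the cost difference is the numerator of both ratios.

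Only 18 centres are randomised, and the Discussion itself calls clinical practice highly heterogeneous. Its answer there is that the multilevel analysis will take this variability into account, but the economic section does not refer to that analysis. Cost-effectiveness and cost-utility are part of the main objective, and the article makes transfer to clinical guidelines conditional on them. A starting difference between the arms could therefore be counted as QALYs or euros gained or lost through coaching.

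**Working it through.** **Inputs from the Sample size section:** SD 14, correlation 0.6 between first and second measurement, ICC 0.05, difference of 5 units, 20% loss, 9 centres of 20 patients per arm. **From Table 2:** visits at 0, 1, 3, 6 and 12 months.

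**Assumptions not in the document:** the QALY measure is a trapezoid area that includes baseline; the correlation is 0.6 between every pair of visits; the 5-unit effect is constant from month 1. All results are on the WOMAC scale.

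**1. The plan's own figure.** SD of change = 14 × √(2 × (1 − 0.6)) = 12.52. This gives 99 per arm, and 99 / 0.8 gives 124. Design effect 1 + 9 × 0.05 = 1.45, and 124 × 1.45 = 179.8, so 180. The plan's figure reproduces. Below I use 20 patients per centre, the number to be recruited from each randomised unit: design effect 1 + 19 × 0.05 = 1.95.

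**2. Chance baseline difference.** SE = √(2 × 14² × 1.95 / 180) = 2.06 points. The 95% range is ±1.96 × 2.06 = ±4.04.

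**3. Carry-over into the area.** The trapezoid weights are 0.042, 0.125, 0.208, 0.375 and 0.250. The slope of the area on baseline is 0.042 + 0.958 × 0.6 = 0.617.

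- One-SE imbalance: 2.06 × 0.617 = 1.27 points.
- Edge of the 95% range: 4.04 × 0.617 = 2.49 points.
- Area effect of a 5-unit benefit from month 1: 5 × 0.958 = 4.79 points.
- Shares of that effect: 1.27 / 4.79 = 27% and 2.49 / 4.79 = 52%.

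With ICC from 0.01 to 0.10 and correlation from 0.4 to 0.8, the share at the edge of the 95% range runs from 28% to 83%. If utility were simply WOMAC/96 (an assumption for illustration), 2.49 points would be 0.026 QALY against an effect of 0.050.

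**4. Precision.** The sum of squared weights is 0.264, so Var(area)/SD² = 0.6 + 0.4 × 0.264 = 0.706. Then R² = 0.617² / 0.706 = 0.539, so baseline explains about 54% of the area variance.

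**5. Check by simulation.** In 4,000 simulated trials (9 v 9 centres of 20, ICC 0.05, correlation 0.6):

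- The SE of the area difference fell from 1.73 unadjusted to 1.14 with baseline adjustment.
- The slope of the estimate on the baseline imbalance fell from 0.63 to 0.01.
- When the intervention arm started more than 2 units worse, the unadjusted estimate averaged 2.90 and the adjusted one 4.78, against a true 4.79.
- Over all runs both estimates averaged close to 4.79.
- If centre effects persist more strongly (centre-level correlation 0.9, assumed), the slopes were 0.76 and 0.13, so adjustment removes most of the dependence but not all.

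**6. Costs.** The document gives no cost SD and no correlation between baseline and follow-up cost. For assumed correlations of 0.3, 0.5 and 0.7, adjustment would remove 9%, 25% and 49% of the variance (the square of each).

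**The case against.** A reader might infer that the plan commits itself to crude differences. The text does not go that far: it never calls them raw or unadjusted. The quoted sentence is the ordinary definition of the ratio, and adjusted mean differences would fit it equally well. A journal article may also leave the choice of covariates to a fuller document. This objection stands against any claim of error. It does not remove the point, because the same article does state change-minus-change, adjustment and a centre random effect for the clinical outcomes, then writes separate formulas for the economic ones.

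A reader might also infer that both ratios are affected throughout. They are not. The cost-effectiveness denominator is an effect, not a QALY difference, and may already be change from baseline under the Statistical analysis section.

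Three more objections stand:

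- Chance imbalance does not bias the unadjusted difference over repeated randomisations. It is part of that difference's standard error, and so belongs in a correctly built acceptability curve.
- It does not pass through in full: about 62% carries over under the stated assumptions, and the 2.5-point figure is the edge of the range, not the typical case.
- The planned descriptive comparison of costs between groups could show a baseline cost imbalance, although showing it would not correct the ratios.

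**Conclusion.** The point holds as an improvement in precision and in protection against conditional bias in the one trial that is run. It does not show an invalid estimator. It applies to the QALY difference and to the cost difference in both ratios.

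For QALYs, the typical (one-SE) imbalance shifts the area by about a quarter of the planned effect, and an imbalance at the edge of the 95% range by about half. These figures depend on the three assumptions listed with the inputs: the plan gives 0.6 only for the first two measurements and does not define the time adjustment of the utilities. For costs the direction of the argument is the same, but its size is unknown.

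**What to change.** In the economic section, state that:

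- the incremental QALY comes from a model with arm, baseline WOMAC (or the utility derived from it) and a centre random effect;
- the incremental cost comes from a model of 12-month post-baseline cost with arm, baseline cost and a centre random effect (the post-baseline wording also settles whether the baseline column counts towards total cost);
- the ratios and acceptability curves are built from these adjusted differences, with the unadjusted differences reported alongside.

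This takes a few sentences and slightly more analysis work, with no extra visits or patients. Patients with missing baseline costs would fall under the multiple imputation already planned. One condition applies: baseline cost is useful as a covariate only if its questionnaire covers a defined period before entry. The article gives no such period, so it should be stated.

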#### Applicability of results

This phase aims to show the effectiveness and cost-effectiveness of the health coaching intervention on quality of life improvement, reduction of pain and overweight and increase of physical activity in people suffering from KO.

### Phase 3: evaluation of the intervention programme

A qualitative evaluation of the intervention will take place after Phase 2 to determine which aspects can be improved and the opinions and experiences of participating professionals and patients.

The participants of the second qualitative study (Phase 3) will be adults with osteoarthritis of the knee and primary care professionals that participated in the coaching intervention arm.

Ten semi-structured interviews will be conducted with patients in the IG to check if the intervention has improved their quality of life, reduced pain, contributed to weight loss or increased physical activity. These patients will also be asked about the suitability of times, adaptability and clarity of the intervention contents. Plurality of discourse will be achieved by interviewing participants of both genders, different ages and educational levels. Four discussion groups of 8–12 primary care professionals involved in osteoarthritis care will be created to analyze attitudes, opinions on the intervention and adaptability to standard clinical practice in primary care. The analytical plan will be as in Phase 1.

